## Abstract

**Background:**

High-risk prescribing, adverse drug events, and avoidable adverse drug event hospitalizations are common. The single greatest risk factor for high-risk prescribing and adverse drug events is the number of medications a person is taking. More people are living longer and taking more medications for multiple long-term conditions. Most on-going prescribing occurs in primary care. The most effective, cost-effective, and practical approach to safer prescribing in primary care is not yet known.

**Objective:**

To test the effect of the Safer Prescribing And Care for the Elderly (SPACE) intervention on high-risk prescribing of nonsteroidal anti-inflammatory and antiplatelet medicines, and related adverse drug event hospitalizations.

**Methods:**

This is a protocol of a cluster randomized controlled trial. The clusters will be primary care practices. Data collection and analysis will be at the level of patient.

**Results:**

Recruitment started in 2018. Six-month data collection will be in 2018.

**Conclusions:**

This study addresses an important translational gap, testing an intervention designed to prompt medicines review and support safer prescribing in routine primary care practice.

**Trial Registration:**

Australian New Zealand Clinical Trials Registry: ACTRN12618000034235 http://www.ANZCTR.org.au/ACTRN12618000034235.aspx (Archived with Webcite at http://www.webcitation.org/6yj9RImDf)

## Introduction

### Avoidable Adverse Drug Events

Adverse drug events (ADEs) and avoidable ADE hospital admissions are common, costing health systems billions of dollars every year [1-7]. Internationally, approximately 7% of hospital admissions result from drug-related problems, of which 59% are considered avoidable through safer prescribing [3,4,8]. Most drug-related admissions are caused by commonly prescribed drugs, notably nonsteroidal anti-inflammatory drugs (NSAIDs), antiplatelet medications, and anticoagulants, which together account for one-third of ADE admissions [3,4,9].

### High-risk Prescribing

High-risk prescribing is prescribing that places patients at increased risk of ADEs. The single greatest predictor of ADEs and high-risk prescribing is the number of medications a person is taking [10]. With demographic ageing, there are increasing numbers of older people prescribed multiple medications for multiple co-existing medical conditions [11]. In New Zealand, approximately 10% of people aged 65 years and older are taking ten or more regular medications, and high-risk prescribing is common, often involving NSAIDs [12-14]. The individual circumstances of a patient may justify high-risk prescribing, but to minimize harm it is necessary that medications are regularly reviewed and stopped or started as appropriate [15].

Most on-going medications are prescribed in primary care. Despite strong evidence to guide safe prescribing, a gap remains between existing evidence and current prescribing practice. Translating research evidence into practice is difficult. There are many barriers to regular medication review in everyday practice [16]. The large variation in prescribing between practices and regions in New Zealand suggests room for improvement [13,17,18].

### Safer Prescribing

In New Zealand primary care, most quality improvement processes are delivered through Primary Health Organisations (PHOs), professional groupings of practices for administrative and quality improvement purposes [19]. The most effective, cost-effective, and practical approach to safer prescribing in everyday practice is not yet known [20,21]. There is evidence to suggest education programmes can improve prescribing but education alone is not enough to induce lasting change [13,22]. Complex interventions as part of ongoing quality improvement programs show the most promise, in particular interventions combining audit and feedback, education, incentive for participation, and patient engagement [20,23-26]. The Australian Veterans’ Medicines Advice and Therapeutics Education Service (MATES) quality improvement program in primary care has shown promising results in the Australian Veterans population, especially when delivering a focused message targeting single medications and less so when delivering a combination of messages targeting general topics such as interactions and potentially inappropriate medications in older people with polypharmacy [24]. The MATES programme is based on sound theoretical underpinnings and delivers 4 interventions per year. The MATES intervention uses practice prescribing audits, patient-specific feedback, education to doctors, and a practice mail-out to selected at-risk patients to encourage their engagement.

### The Safer Prescribing and Care for the Elderly (SPACE) Intervention

Adapted from the Australian Veterans’ MATES programme, we developed the Safer Prescribing and Care for the Elderly (SPACE) intervention to prompt medication reviews and support safer prescribing in the New Zealand primary care context. We recently piloted the SPACE intervention in two New Zealand primary care practices in preparation for this proposed randomized trial, focusing on the topic of NSAIDs and antiplatelet prescribing. This topic was chosen because these drugs are commonly prescribed and are associated with serious ADEs including bleeding and renal impairment. The SPACE intervention was found to be feasible to implement using existing primary care structures and both acceptable and useful to patients, doctors, and the PHO clinical advisory pharmacists [27]. In the pilot study, we developed practice audit queries to identify patients with high-risk prescribing of NSAIDs and/or antiplatelet medications; integrated the SPACE intervention into practice management software; developed processes to collect, encrypt, and link study data; and derived information for calculating sample sizes for the randomized trial.

### Objectives

We will assess whether the SPACE intervention can reduce the rate of high-risk prescribing of NSAIDs and/or antiplatelet medications and related ADE hospitalizations over 12 months using existing PHO infrastructure and systems in New Zealand primary care.

### Trial Design

We will conduct a cluster randomized control trial. The clusters will be primary care practices. Data collection and analysis will be at the level of patient.

## Methods

### Setting

The study will be conducted in primary care practices in Auckland and Northland, New Zealand.

### Eligibility Criteria

Primary care practices will be eligible to participate if:

The practice is based in the Auckland or Northland region of New Zealand and has not recently participated in a similar NSAID audit exercise or taken part in the pilot for the SPACE trialThe practice uses electronic practice management software compatible with our data collection systemsThe practice has fewer than 15,000 enrolled patientsAll physicians in the practice consent to participate

The study will target all physicians working in participating practices since patients can receive a prescription from any physician in a practice.

Patient inclusion criteria:

Patients of any age (“vulnerable patients”) will be included in the study if, at baseline, they fulfil one or more of the following inclusion criteria as listed in Table 1 that puts them at increased risk of an ADE related to NSAIDs and/or antiplatelet medications.Participants are “vulnerable patients” at baseline; that is, those patients at increased risk of gastrointestinal, renal or cardiac adverse events related to NSAIDs and/or antiplatelet medications (Table 1).

**Table 1 table1:** Categories of vulnerable patients and high-risk prescribing of NSAIDs and antiplatelet medications [23]. ADE: adverse drug event.

Type of adverse drug event	Risk factor making patients vulnerable (at increased risk of ADE)	High-risk prescribing
Gastrointestinal	Prior peptic ulcer	In patient with prior peptic ulcer, NSAID or aspirin without gastro-protection
	75 years and older	In patient 75 years and older, NSAID without gastro-protection
	65 years and older prescribed aspirin	In patient 65 years and older taking aspirin, NSAID without gastro-protection
		In patient 65 years and older taking aspirin, clopidogrel without gastro-protection
	Prescribed oral anticoagulant	In patient taking an oral anticoagulant, NSAID without gastro-protection
		In patient taking an oral anticoagulant, aspirin or clopidogrel without gastro-protection
Renal	Prescribed both renin-angiotensin system blocker and diuretic	In patient taking both renin-angiotensin system blocker and diuretic, NSAID
	Chronic kidney disease (Estimated Glomerular Filtration Rate[eGFR] <60)	In patient with chronic kidney disease (eGFR <60), NSAID
Cardiac	Heart failure	In patient with history of heart failure, NSAID

All data collected on patients is anonymized prior to leaving the practice using a unique identifier (National Health Index number) to enable linking of clinical data over time and linking to hospitalization data.

### Intervention

The SPACE intervention is designed to prompt medication reviews and support safer prescribing decisions in primary care practice. The intervention comprises a practice audit to identify for each doctor a list of their patients with high-risk prescribing for the chosen topic; an outreach visit from a clinical advisory pharmacist to physicians to provide education about the prescribing topic and to go through with each physician their list of patients identified as having high-risk prescribing; a tick-box for physicians to indicate the action they will take in response to the feedback for each patient (“review medications + patient mail-out,” “review medications + no mail-out,” or “no action”); and a mail-out from the practice to patients selected by physicians with information about their medications and a letter encouraging them to discuss their medications when they are at the practice next seeing their physician [27]. All prescribing decisions are made as usual by the doctor in discussion with the patient. The individual circumstances of the patient may justify high-risk prescribing and, after review, the prescribing may or may not be changed. The prescribing topic for the trial is the prescribing of NSAIDs and antiplatelet medications.

Control practices will deliver care as usual. If the SPACE intervention is shown to be effective, we aim to deliver the intervention to control practices after 12 months.

All practices and doctors will participate as usual in PHO quality improvement initiatives and medical education activities. See Figure 1 for the flow of practices through the study.

### Outcome Measures

Assessment time-points will be baseline, 6 months, and 12 months. The outcomes of interest are the difference between intervention and control groups at 6 months controlling for baseline, and the difference between intervention and control groups at 12 months.

The primary outcome measure is:

The difference in proportion of the participants (those vulnerable at baseline) receiving high-risk prescribing of NSAID and/or antiplatelet medications between the control and intervention groups at 6 months. That is, the proportion of “vulnerable-at-baseline patients” (with gastro-intestinal, renal, or cardiac risk factors) receiving high-risk prescribing of NSAID and/or antiplatelet medications at 6 months according to the definitions listed in Table 1. Whether difference in proportion between the two groups is sustained at 12 months will also be examined. Participants will be considered to have high-risk prescribing at each time-point if they fulfil any of the high-risk prescribing criteria set out in Table 1 in the 14 weeks leading up to each time-point.

**Figure 1 figure1:**
[figure not shown]
Flow of practices through the randomized control trial.

Secondary outcome measures include:

The difference in proportion of study participants at increased risk of gastrointestinal ADEs according to the definitions listed in Table 1 receiving gastrointestinal high-risk prescribing of NSAID and/or antiplatelet medications between the control and intervention groups at 6 months.The difference in proportion of study participants at increased risk of renal ADEs according to the definitions listed in Table 1 receiving renal high-risk prescribing of NSAID medications between the control and intervention groups at 6 months.The difference in proportion of study participants at increased risk of cardiac ADEs according to the definitions listed in Table 1 receiving cardiac high-risk prescribing of NSAID medications between the control and intervention groups at 6 months.The difference in proportion of study participants (vulnerable patients), and those with high risk prescribing, admitted for related adverse drug events (gastrointestinal ulcer or bleeding, acute kidney injury, and heart failure) between the control and intervention groups during the 12 months after baseline for the intervention. Hospitalization data will be linked to primary care patient data by encrypted National Health Index.The difference in proportion of vulnerable patients in the practice overall receiving high-risk prescribing of NSAIDs and/or antiplatelet medications between the control and intervention groups at 6 months. This will include newcomers to the practice and practice patients who were not vulnerable at baseline but were at 6 months and/or 12 months.

Whether difference in proportion between the 2 groups is sustained at 12 months will also be examined for secondary outcomes 1, 2, 3, and 5 months.

These outcomes have been used in similar trials previously [23]. Data will also be collected to enable a subsequent cost-effectiveness evaluation of the intervention from a societal and health funder perspective. The cost-effectiveness of the intervention will be measured as the cost per reduction in high-risk prescribing and cost per reduction in hospitalizations from the health funder (District Health Board) perspective. The data collected will include the cost of delivering the intervention (including pharmacist and doctor time for the feedback outreach session, travel time and costs for the outreach visit, audit time and cost); cost of medications; cost of hospitalizations.

### Sample Size

The sample size calculation for this study is based on previous trials demonstrating a clinically relevant 25-45% relative risk reduction in the proportion of high-risk prescribing, [23,25] one trial of which also demonstrated how such reduction (3.7% to 2.2%) in high-risk prescribing can translate to significant reductions in hospitalizations due to bleeding complications [23]. Based on the local pilot data, we estimated an average of 200 “vulnerable patients” per practice and an 8% high-risk prescribing rate [28]. We estimated an intracluster correlation coefficient of 4.68 x 10^-7^ for the primary outcome based on a cluster randomized trial examining similar outcome of NSAIDs prescribed to patients with a history of peptic ulcer and not prescribed gastro-protection [25]. Assuming approximately 12% of patients would be lost to follow-up over the 12 month study period, data from 8000 patients from 40 practices (20 practices in each group) with an average of 200 vulnerable patients per practice would be required to detect a statistically significant difference of 6% in the intervention group and 8% in the control group of high-risk prescribing at 12 months (*P*=.90, alpha=.05).

### Recruitment

Practices will be purposively sampled and recruited, aiming to include both medium sized (3000-7999 enrolled patients) and smaller practices (0-2999 enrolled patients) in the Auckland and Northland regions. Practices and physicians will be invited by a colleague using a comprehensive list of practices. Consent for participation will be at the practice and physician level. Written informed consent will be obtained from all participating physicians. Participants, ‘vulnerable patients’, will be identified using a standard query applied to the practice enrolled population. Consent will not be sought from individual patients because outcomes data are collected in routine patient care and will be anonymised prior to extraction for analysis and linking.

### Assignment of Interventions: Randomization

Practices will be randomized 1:1 to intervention or control. Randomization will be stratified by practice location (Auckland vs Northland) and practice size (medium [3000-7999 enrolled patients] and smaller practices [0-2999 enrolled patients]). Block randomization will be carried out using randomly varying block sizes of 2, 4, and 6. Random sequence generation and allocation of randomization will be undertaken by a statistician not involved in recruitment or baseline data extraction.

### Analyses

Analyses will be performed according to the intention-to-treat principle, with the use of mixed-effect models to account for clustering in the data. The primary and secondary outcomes will be analyzed using generalized linear mixed effect model, GLIMMIX, with the individual as the unit of analysis and the practice included as the random effect to control for the effects of clustering. GLIMMIX with Group x Time interaction will be used to assess the overall difference between intervention and control. The model will adjust for the stratification factors including practice location (Northland or Auckland) and practice size. Baseline covariates including (age, sex, and baseline number of long-term medications) will be adjusted if appropriate.

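### The Group x Time model names practice as its only random effect, so repeated records on the same patients are treated as independent and the primary test is conservative and under-powered

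*Protocol article*

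**What the plan says.** Under Outcome Measures, the schedule is stated as "Assessment time-points will be baseline, 6 months, and 12 months". The primary outcome is defined on a fixed cohort, the patients vulnerable at baseline, and their status is derived afresh each time: "Participants will be considered to have high-risk prescribing at each time-point if they fulfil any of the high-risk prescribing criteria". The 6-month contrast of interest is "the difference between intervention and control groups at 6 months controlling for baseline". Under Eligibility Criteria, a patient identifier is kept "to enable linking of clinical data over time and linking to hospitalization data", so each patient's records can be joined.

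Under Analyses, primary and secondary outcomes go into a generalized linear mixed model "with the individual as the unit of analysis and the practice included as the random effect to control for the effects of clustering". The next sentence gives the test: "GLIMMIX with Group x Time interaction will be used to assess the overall difference between intervention and control". The fixed effects listed are the stratification factors and, if appropriate, age, sex and number of long-term medications. Baseline high-risk prescribing status is not listed.

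Under Sample Size, the calculation compares two proportions at one time-point. It requires "data from 8000 patients from 40 practices (20 practices in each group) with an average of 200 vulnerable patients per practice" in order to "detect a statistically significant difference of 6% in the intervention group and 8% in the control group of high-risk prescribing at 12 months".

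**The concern.** A Group x Time term needs at least two records per patient. If practice is the only random effect, two records of one patient are assumed to be no more alike than records of two different patients in that practice. Long-term prescribing tends to persist, so that assumption is unlikely to hold.

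The interaction is a contrast of changes. Positive correlation between a patient's baseline and 6-month status makes the change less variable. A model that ignores the correlation therefore reports too large a standard error. At stake is a primary p-value and confidence interval that are too cautious, and a trial that may miss the effect it was sized to find.

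The three sections also do not describe one analysis. Outcome Measures asks for a baseline-adjusted 6-month difference, Sample Size plans a single-time-point comparison, and Analyses names a longitudinal interaction.

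**Working it through.** **Reproducing the plan's figure.** Inputs from Sample Size: 8% vs 6%, alpha 0.05 (taken as two-sided), power 0.90, intracluster correlation (ICC) 4.68 x 10^-7, 200 patients per practice, 12% loss.
- Design effect: 1 + 199 x 4.68 x 10^-7 = 1.0001.
- Two-proportion formula with continuity correction: 3518 per arm, 7036 in total. Dividing by 0.88 and rounding up per arm gives 7998. Without the correction: 3419 per arm, 7772 in total.

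The stated 8000 reproduces, so the sample size arithmetic is not at issue. Analysable patients: 8000 x 0.88 / 2 = 3520 per arm. The simple comparison then has 91% power.

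**Standard error of the interaction, risk-difference scale.** Let v = 0.07 x 0.93 = 0.0651 (the average prevalence), n = 3520, and rho the within-patient correlation between baseline and 6 months. The article gives no rho, so 0.3, 0.5 and 0.7 are assumed. Practice variation is negligible at the stated ICC.
- Stated model: SE = sqrt(4v/n) = sqrt(0.2604/3520) = 0.0086, whatever rho is.
- True: SE = sqrt(4v(1 - rho)/n).
- Ratio: 1/sqrt(1 - rho).
- Actual type I error: 2 x [1 - Phi(1.96 x ratio)].
- Power, stated model: Phi((0.02 - 1.96 x 0.0086)/true SE).
- Power, correlation modelled: Phi(0.02/true SE - 1.96).

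| rho | true SE | SE ratio | actual type I error | power, stated model | power, correlation modelled |
|---|---|---|---|---|---|
| 0.3 | 0.0072 | 1.20 | 1.9% | 67% | 79% |
| 0.5 | 0.0061 | 1.41 | 0.6% | 70% | 91% |
| 0.7 | 0.0047 | 1.83 | 0.03% | 75% | 99% |

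**Same check on the log-odds scale.** The model SE is 0.129 throughout. The true SE is 0.108, 0.091 and 0.071 (ratios 1.19, 1.41, 1.82). Power is 70%, 73% and 79% with the stated model, and 82%, 92% and 99% with the correlation modelled.

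**Simulation of the stated logistic model.** Settings: 40 practices x 176 patients x 3 times, 250 runs per setting, assumed practice SD 0.1 on the logit scale. Under the null, model-to-empirical SE ratios were 0.99, 1.23, 1.42 and 1.80 at rho 0, 0.3, 0.5 and 0.7. Rejection rates were 4.8%, 2.0%, 0.8% and 0.0%. With the planned effect, power was 65%, 71%, 71% and 76%.

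**Practice drift, the opposite direction.** Let m = 176 and let c be the correlation of a practice's level over time (assumed). The variance of change in a practice mean, in units of v, is:
- true: 2 x ICC x (1 - c) + 2 x (1 - ICC) x (1 - rho)/m
- working model: 2 x (1 - ICC x c)/m

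With rho = 0.5:

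| ICC | c | true | working | approximate type I error |
|---|---|---|---|---|
| 4.68 x 10^-7 | 0.6 | 0.0057 | 0.0114 | 0.6% |
| 0.01 | 0.8 | 0.0096 | 0.0113 | 3.4% |
| 0.02 | 0.8 | 0.0136 | 0.0112 | 8% |
| 0.02 | 0.6 | 0.0216 | 0.0112 | 16% |
| 0.05 | 0.8 | 0.0254 | 0.0109 | 20% |

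Setting the two variances equal gives a break-even ICC = rho/[(1 - c)m - 1 + rho + c]. At rho 0.5 that is 0.5/35.5 = 0.014 for c = 0.8, and 0.5/70.5 = 0.007 for c = 0.6.

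**The single-record alternative.** With baseline status as a covariate, SE is approximately sqrt(2v(1 - rho^2)/n) = 0.0058, 0.0053 and 0.0043 at rho 0.3, 0.5 and 0.7. Power is Phi(0.02/SE - 1.96) = 93%, 97% and over 99%. At rho = 0 it is 91%.

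**The case against.** The strongest reply is that this is a short analysis section in a journal article. The sentence on practice explains how clustering is handled and does not exclude a within-patient covariance. The software can carry one as a residual structure, which need not be called a random effect, and an unseen analysis plan may specify it. That stands as a limit on certainty. It does not remove the point: the article states its random effect in the singular, gives practice clustering as the reason, and pairs it with a Group x Time test. Followed as written, that gives a wrong standard error.

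A second reply is that the first sentence on the mixed model, read with the baseline-controlled 6-month outcome, could mean one record per patient. That is possible, but the next sentence assigns the overall comparison to the interaction, and baseline status is not a listed covariate. The text does not settle which analysis gives the primary p-value.

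Third, not all of the shortfall from 90% comes from the missing term. At rho 0.3 a correctly modelled change contrast itself reaches only 79–82%; the omission then takes it to 67–70%. This is right, and the cost of choosing a change contrast should be kept separate.

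A reader might infer that the test also inflates false positives, or that its error could run either way with equal support. The article does not support this. Inflation needs practice drift together with an ICC of the order of 0.01 to 0.02 or more, tens of thousands of times the stated value in most settings considered, and no such figures are given. Whether the stated ICC is itself credible is a separate question.

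**Conclusion.** The point holds as a fault in the stated model, with one supported direction. For the baseline-to-6-month interaction, ignoring positive within-patient correlation makes the standard error about 1.2 to 1.8 times too large, makes the test conservative, and leaves power at about 67–79% instead of 90%. The range covers both scales of calculation and rests on assumed correlations of 0.3 to 0.7, on 3520 analysable patients per arm, and on the article's rates and ICC. The standard error is right only if a patient's prescribing status is uncorrelated over time.

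Inflated type I error from practice-by-time variation remains a conditional risk and is not a finding on this document's own figures. The point does not apply to hospitalization over 12 months, which has one record per patient.

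**What to change.** Make the primary analysis the 6-month outcome with one record per patient: a practice random intercept, the stratification factors, and baseline high-risk prescribing status as a covariate. Analyse 12 months in the same way. This agrees with the baseline-controlled contrast under Outcome Measures and with the single-time-point form of the sample size calculation.

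If the longitudinal Group x Time model is kept, add a patient-level random effect or a within-patient covariance, and preferably a practice-by-time random effect with degrees of freedom based on the number of practices.

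The cost is analysis-plan wording and a few lines of model code, settled before analysis, with no new data. If the analysis plan already contains the within-patient term, the sponsor need only bring the published description into line with it.
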